### Quality control

Before the start of the trial, a non-disclosure agreement needs to be signed of all participants. They will be required to keep the contents of the intervention strictly confidential to ensure each group will receive the game at the specified time. Pre-testing will be conducted before the study begins, and the formal study protocol will be adjusted based on the results of the preliminary tests. After completing the research, each participant will receive a cash prize ranging from 20 to 100 RMB through a lottery.

### Outcomes and data collection

The primary outcomes are medication adherence, CD4( +) T cell count, and HIV viral load. Medication adherence will be assessed by calculating the Medication Possession Ratio (MPR) [40], which will be calculated by the following formula:$$MPR=\frac{days\mathrm{cov}eredwiththesumofdailydoses}{daysonART}$$

MPR is defined from 0 to 1, with closer to 1, indicating higher the adherence. In addition, The CPCRA 7-day recall adherence questionnaire [41] will be used to assess the medication adherence. Within the questionnaire, participants will be asked to recall the proportion of the prescribed medication in the past 7 days (100%, 80%, 50%, 20%, 0%) and the amount of missed medication in the past 3 days, 7 days and 30 days. CD4( +) T cell count, HIV viral load will be obtained by biochemical testing, and the testing will be carried out in a medical unit with testing qualifications. Participants with less than 400 copies/mL will be coded as being virally suppressed, while participants with viral loads of 400 or more copies/mL will be classified as not being virally suppressed [42].

Secondary outcomes are ART-related knowledge, ART-related skills, psychological resilience, self-discrimination. ART-related knowledge will be assessed by ART-related knowledge questionnaire [
43], which was developed in Chinese with 21 items, each item has a correct answer and scored one point. A higher the score means higher the ART-related knowledge. ART-related skills will be assessed through a self-made questionnaire with 20 items, one point being allocated for a correct answer. The higher the score, means higher the ART-related skills. Psychological resilience will be assessed by the Resilience Scale for PLHIV [44], which was developed by our study team, including three dimensions and 29 items, one point for a correct answer. A higher the score means higher psychological resilience. Self-discrimination will be assessed by the Chinese version of Berger HIV stigma scale [45], which has 18 items, each item scored on a 4-point scale (from "strongly disagree" to "strongly agree" with a score of 1 to 4). A higher the score means higher self-discrimination.

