### Sample size calculation

The sample size was performed using the formula developed by Hemming [39]. The basic parameters for sample size calculation are based on the mean rate of adherence to ART at one week (81.1%) [9], assuming that the ART adherence of the intervention group would reaches 95%. The significance level of the test is α=0.05, the test power is 1-β=0.9, the coefficient of variation is ρ=0.15, the number of observation periods is t+1=7, the number of steps is t=6, the number of clusters is k=4, and N1 is calculated based on the sample size of the two groups. PASS software was used to calculate the initial sample size N1=220. According to the following formula:$$\begin{array}{c}a=2k\left(t-\frac{1}{t}\right)\rho \left(1+\frac{t}{2}\right)\\ b={3N}_{1}\left(1-\rho \right)\rho \left(1+t\right)-2k\left(t-\frac{1}{t}\right)\left(1-\rho \right)\\ \begin{array}{c}c={3N}_{1}{\left(1-\rho \right)}^{2}\\ m=\frac{-b\pm \sqrt{{b}^{2}-4ac}}{2a}\\ N=\mathrm{m}\times \left(t+1\right)\times k\end{array}\end{array}$$

The required sample size for each group is calculated to be 140. Considering a potential 20% loss to follow-up, the final sample size for each group is 175, and the total sample size is 700.

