### Data analysis

All data will be uniformly entered by Epidata 3.1. And SPSS 26.0 statistical software will be used for analysis. The categorical data will be described by composition ratio and compared by chi-square test; quantitative data will be described by mean ± standard deviation and compared by Analysis of Variance; Generalized estimating equations models and linear mixed-effect (LME) models will be used to analyze the effect of game-based health education on ART medication adherence, CD4( +) T cell count, ART-related knowledge, psychological resilience, and self-discrimination. Mixed effects logistic regression models will be used for HIV viral load outcomes. Difference-in-difference analysis will be used to evaluate the change in the intervention groups excluding the effect of the changing over time. The differences are statistically significant with P ≤ 0.05.

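### Three unordered primary outcomes and two undesignated adherence measures share one unadjusted P ≤ 0.05 with no success rule, so the planned 5% error rate is not secured

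*Protocol article*

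**What the plan says.** Outcomes and data collection, in agreement with the Abstract, states: "The primary outcomes are medication adherence, CD4( +) T cell count, and HIV viral load". No order or hierarchy is given.

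Adherence is then measured twice. MPR comes first and has a formula. The section adds that the CPCRA 7-day recall questionnaire "will be used to assess the medication adherence" as well. Neither is designated as the measure that decides.

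Data analysis closes with one rule for everything: "The differences are statistically significant with P ≤ 0.05". It mentions no adjustment, no testing order and no requirement that all primary outcomes succeed.

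Sample size calculation plans one comparison, adherence of 81.1% against an assumed 95%: "The significance level of the test is α=0.05, the test power is 1-β=0.9". All three hypotheses under Study design are about ART adherence. None names the measure, and none covers CD4 count or viral load.

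**The concern.** The 5% in the sample size section belongs to a single adherence test. The outcome section offers three primary outcomes, or four primary measures once adherence is counted twice, and the analysis section lets each be called significant at 0.05. If any one of them can carry the conclusion, the trial has several chances of a false positive and its error rate is no longer 5%.

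Interpretation is also at stake. Recall-based adherence could improve while MPR or viral suppression does not. The protocol gives no way to say whether that trial is positive, although the Discussion expects the trial to show whether the game is effective.

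**Working it through.** **Inputs.** Three primary outcomes and two adherence measures (Outcomes and data collection). Threshold 0.05 (Data analysis). α = 0.05, power 0.90, 81.1% against 95%, ρ = 0.15, t = 6, k = 4, N1 = 220 and 20% loss (Sample size calculation). Correlations between the test statistics are not given, so they are assumed below.

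**1. The plan's own figures: one adherence test.** The two-proportion formula with unpooled variance and two-sided α = 0.05 gives, per arm:

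(1.960 + 1.282)² × (0.811×0.189 + 0.95×0.05) / 0.139² = 109.2, rounded up to 110.

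So N1 = 220, as stated. The protocol does not state sidedness, but two-sided reproduces N1 and one-sided does not (178 to 184). The printed quadratic has only negative roots (−0.91 and −18.71). With the sign of *a* reversed, m = 20.45. Rounded to 20 this gives 20 × 7 = 140 per group, 140/0.80 = 175 after loss, and 4 × 175 = 700. The printed sign is a separate matter. What counts here is that 700 rests on one adherence test at 0.05.

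**2. Error rate if any one significant test counts as success.** With n independent tests and no true effect, P(at least one false positive) = 1 − 0.95ⁿ. Under any dependence it cannot exceed n × 0.05. The correlated values come from simulating equicorrelated normal test statistics (1,000,000 draws).

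| Tests | Independent | Correlation 0.3 | 0.5 | 0.8 | Upper bound |
|---|---|---|---|---|---|
| 3 (one per primary outcome) | 1 − 0.95³ = 14.3% | 13.6% | 12.5% | 9.9% | 15% |
| 4 (adherence counted twice) | 1 − 0.95⁴ = 18.5% | 17.4% | 15.6% | 11.4% | 20% |

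**3. Narrowest reading: only adherence decides, but either measure may.** 1 − 0.95² = 9.75% if independent, with an upper bound of 10%.

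**4. Opposite reading: all primary outcomes must be significant.** The error stays at or below 5%. The 90% power, however, was computed for adherence alone, so it is not the power to succeed on all three.

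**5. Cost of keeping every test primary with Bonferroni** (same formulas, power 0.90, m rounded to the nearest integer):

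- Three tests, α = 0.05/3 = 0.0167: N1 = 282 and m = 26.4, rounded to 26. That is 26 × 7 = 182 per group, 182/0.80 = 227.5, rounded up to 228, and 4 × 228 = 912 in total.
- Four tests, α = 0.05/4 = 0.0125: N1 = 298 and m = 27.9, rounded to 28. That is 196 per group, 196/0.80 = 245, and 980 in total.
- With N1 kept at 220, power on adherence falls from 90% to about 80% (three tests) or 78% (four).

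**The case against.** The strongest reply is that this is a condensed article. Testing order and multiplicity rules are often left to an analysis plan, and the threshold sentence may be a routine closing line. That limits the point but does not remove it. The article does more than stay silent: it names three primary outcomes and fixes one threshold for all differences, against a sample size built on one.

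Several stronger readings are tempting, and the text does not support them:

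- *The 5% fails outright.* This needs a rule that any single significant result makes the trial positive. The protocol permits that rule but does not state it. Nor should the outcomes be called co-primary: in the strict sense all must succeed, and then there is no inflation.
- *The error is 14% to 19%.* Those are the independent-test values. The two adherence measures address one construct, and the Background links adherence to viral suppression and CD4 count, so some correlation is likely. The hypotheses also concern adherence only. On that reading at most 10% is at issue, and MPR, given first and with a formula, looks like the lead measure, though the protocol does not designate it.
- *CD4 count and viral load have no power.* No power calculation is given for them. Their power with 700 participants is unknown, not nil.
- *Repeated visits and four groups inflate the error further.* The planned generalized estimating equations and mixed models can give one intervention effect across visits. Separate tests at each visit are not stated.

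**Conclusion.** The point holds in conditional form. Three primary outcomes without order, two adherence measures without a deciding one, and a common P ≤ 0.05 do not secure the 5% on which the sample size is based.

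The size depends on two things the protocol does not give: the success rule and the correlations. If any one measure suffices, the false-positive chance runs from about 10% (three tests, correlation 0.8) to about 19% (four independent tests). If only adherence decides, it is at most 10%. If all outcomes must succeed, it is at most 5%, but the stated 90% power then does not describe the trial's chance of success. Under each of these readings, the outcome, analysis and sample size sections do not fit together.

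**What to change.** Designate one adherence measure as deciding, for example MPR. Take its single intervention-effect estimate from one of the planned models, named in advance, as the primary test at two-sided 0.05. Only if that test succeeds, test viral suppression, CD4 count and the CPCRA measure in a stated fixed sequence, or with Holm. Label the hypotheses on timing and on long-term maintenance as secondary.

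This leaves α for the adherence test at 0.05, so the planned 700 and the power on adherence do not change, unlike the Bonferroni totals of 912 or 980. Data collection also stays as planned, provided the primary test is the model's overall intervention effect. Fixing it at one time since ART start is a different matter. Study design and Intervention design schedule assessments relative to each group's intervention start, so the existing visits may not supply that time point in every group.

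The cost is that CD4 count and viral load no longer support a positive conclusion on their own. The protocol wording would change, and the registered primary outcomes would need updating to match.

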### Data analysis

All data will be uniformly entered by Epidata 3.1. And SPSS 26.0 statistical software will be used for analysis. The categorical data will be described by composition ratio and compared by chi-square test; quantitative data will be described by mean ± standard deviation and compared by Analysis of Variance; Generalized estimating equations models and linear mixed-effect (LME) models will be used to analyze the effect of game-based health education on ART medication adherence, CD4( +) T cell count, ART-related knowledge, psychological resilience, and self-discrimination. Mixed effects logistic regression models will be used for HIV viral load outcomes. Difference-in-difference analysis will be used to evaluate the change in the intervention groups excluding the effect of the changing over time. The differences are statistically significant with P ≤ 0.05.

### Ethical approval and clinical trial registration

This study has been approved by the Ethics Committee of The Affiliated Hospital of Southwest Medical University, with the approval number KY2022163. And has been registered at Chinese Clinical Trial with the registration number ChiCTR2200059766. The Ethics Committee will audit the conduct of the trial, and have the right to make the decision to terminate the trial. The process will be independent from investigators and the sponsor. The study data will be uploaded to the China Clinical Trials Registry after the study is complete.

## Discussion

The adherence of ART is fine in developed countries or areas, but which is poor in the southwest of China [46]. Many HIV-infected could not initiate ART immediately, with where the economy is relatively backward, people are poorly educated, and AIDS-related knowledge is lacking [47]. Especially for young people newly diagnosed with HIV in those areas, it is hard for them to start ART or adhere ART for long term [18, 19]. As many young people at the time they diagnosed with HIV, the immune damage was not severe and there were no clinical symptoms [48]. In addition, young people's social needs lead to their fear of being found to be taking ART medicine [49]. Therefore, it is needed to carry out HIV and ART-related health education among newly diagnosed HIV-infected people to improve their adherence of ART.

With the development of science and technology, AIDS health education has changed from traditional to modern ways. Among them, game-based intervention has become a significant method to change healthy behaviors [50, 51]. In our previous studies, an AIDS educational game called AIDS Fighter· Health Defense was developed, and a randomized controlled trial was conducted and proved that this game has a good education effect on AIDS prevention for young students. Students have good comments on the game and believe it could help them learn more about AIDS [36]. In this study, we would like to evaluate the effect of this game to improve ART adherence of young people newly diagnosed with HIV. And provide evidence for game-based education to improve ART adherence in China.

Someone diagnosed with HIV may be shocked and frustrated, especially young people who need to live with HIV for a long time [52]. It will take a while for them to adjust to the fact of being infected with HIV and accept to start ART [53], but they usually do not get that time and receive AIDS education and are required to start ART at the time of diagnosis in China [54]. This might be one of the reasons why adherence to ART sharply declines in the short term after initiation [55]. ART-related education could be more effective in maintaining long-term ART adherence in newly diagnosed people with HIV after they accept the fact of infection and are willing to learn AIDS-related knowledge [56, 57]. But it is limited to know how long it will take for young people infected with HIV to recover psychologically after infection. Therefore, we designed the protocol to find the optimal time point of intervention for ART adherence education. In this study, game-based education will be added to regular AIDS education to improve ART adherence of newly diagnosed young people with HIV. A stepped-wedge design randomized controlled trial will be conducted to evaluate the effect of game-based education and figure out when to start game-based education could be more effective. This could provide a reference for whether HIV-infected people need to be given some time for self-adjustment before receiving AIDS education and find out the difference in educational effect between different self-adjustment times.

We believe with the development of this study we will discover whether game-based education is effective in improving ART adherence in newly diagnosed young people with HIV. We could develop an AIDS education gamification method for China and other countries to improve the ART adherence of newly diagnosed young people with HIV. Beyond that, we will discover whether starting AIDS education at different times makes a difference and ascertain when to start AIDS education more effectively in China. This could be an innovation in AIDS education.

## Data Availability

The data collected in this study will be published in papers after the study is completed.

## Abbreviations

AIDS: Acquired Immune Deficiency Syndrome
ART: Antiretroviral therapy
CPCRA: Community Programs for Clinical Research on AIDS
HIV: Human Immunodeficiency Virus
MPR: Medication Possession Ratio
LME: Linear mixed-effect
PLHIV: People Living with HIV
PrEP: Pre-exposure prophylaxis
WHO: World Health Organization
